
##### Safety evaluation

2.8.3.3

All adverse events will be documented in the Case Report Form. The detailed description on the categories, severity, frequency, and correlation with the treatment of the adverse events will be collected by patients themselves and evaluators. Adverse events related to acupuncture (severe pain, local hematoma, infection and abscess, and broken needles during the treatment), including discomfort after treatment, will be recorded in time in detail. Adverse events irrelevant to the treatment will also be recorded in detail.

##### Sample size calculation

2.8.3.4

The sample size was calculated based on the primary outcome, which is the proportion of participants with a reduction of 50% or more on their mean 24-hour HF score from baseline at week 6. The proportion of participants with at least a 50% decrease from baseline in 6 weeks was assumed to be 55% in the EPN group and 28% in the waitlist control group based on the previous research.^[9,23]^ Therefore, a sample size of 49 in each group is estimated to detect the group difference of 27%, with 80% power and a 2-sided significance level of 5%. A total of 122 patients (61 in each group) will be recruited for the study, assuming drop-off rate of 20% in the follow-up.

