### Recruitment strategies

2.2

Patients are planned to be recruited via advertisements in websites and posters from hospitals and communities. All potentially eligible women with hot flashes will be invited to the trial, continued with a series of history taking, questionnaire, HF diary, ultrasound of uterus and ovaries, and laboratory examination to screen and enroll the patients, as recommended by ACOG guideline.^[2]^ Eligible patients will be randomly divided into EPN group and waitlist control group.

Personal information including age, marriage, menstrual, education background, and medical history are cautiously recorded. Hot flashes diaries are applied to assess the severity of HF symptoms. Menopause rating scale (MRS) and Menopause-Specific Quality of Life Questionnaire (MENQOL) are applied to assess the influence on the quality of life. Patients’ expectance and confidence evaluation toward EPN will also be evaluated before the trial. The duration of the trial is 31 weeks for each patient, including 1-week baseline assessment (week 0–1), 6-week treatment period (week 1–6), and 24-week follow-up (week 7–30).

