### Randomization and allocation concealment

2.3

Eligible patients will be randomized into the EPN group or the waitlist group in a 1:1 ratio with a variable block. Randomization sequence numbers will be produced by SAS 9.4 and kept in sealed opaque envelops. The envelops will be numbered and opened sequentially in accordance with the enrollment order.

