##### Primary outcome measure

2.8.3.1

The primary outcome is the proportion of patients with a reduction of 50%^[17]^ or more on the mean 24-hour HF score from baseline at week 6.

Participants will record the frequency and severity (mild, moderate, severe, and very severe) of each HF in 7-day HF diary (HFD). It was a feasible and acceptable tool for women to complete over 7 days with minimal missing data.^[14,15]^ HF score will be calculated based on the frequency and severity of each HF recorded in 7-day HFD to evaluate the severity of general symptoms, as follows: mean 24-hour HF score = (1 × number of mild HF + 2 × number of moderate HF + 3 × number of severe HF + 4 × number of very severe HF)/Number of days reported.

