### Statistical analysis

2.9

The primary outcome of 24-hour mean HF score will be compared between the EPN group and the waitlist control group at week 6. Those who did not feedback data of HF score at week 6 will be regarded as patients whose reduction does not reach 50%. A *P* value <.05 will be considered statistically significant. Subgroup analysis will be conducted among perimenopausal patients and postmenopausal patients.

Continuous data will be presented as mean ± standard deviation when normally distributed, or be presented as median (interquartile range) when not normally distributed. Categorical data will be presented as the number and percentage of participants. Statistical comparisons will be performed by Student *t* test or Wilcoxon rank sum test for continuous data and by X^2^-test or Fisher exact test for categorical data. Data will be analyzed using SPSS software V.22.0 (IBM SPSS Statistics; IBM Corp, Somers, NY).

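### Inflating 49 to 61 per arm does not preserve the stated 80% power, because patients missing at week 6 are analysed as non-responders; power is about 72–74% if the full 20% is missing by then

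*Protocol article*

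**What the plan says.** The primary endpoint is binary. Under Primary outcome measure: "The primary outcome is the proportion of patients with a reduction of 50" per cent or more in the mean 24-hour hot flash score from baseline at week 6.

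The Sample size calculation section is based on that endpoint. The response proportion "was assumed to be 55% in the EPN group and 28% in the waitlist control group based on the previous research", and "a sample size of 49 in each group is estimated to detect the group difference of 27%, with 80% power and a 2-sided significance level" (the level being 5%). It then raises the number: "A total of 122 patients (61 in each group) will be recruited for the study, assuming drop-off rate of 20% in the follow-up".

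The Statistical analysis section fixes what happens to patients without the week-6 score: "Those who did not feedback data of HF score at week 6 will be regarded as patients whose reduction does not reach 50" per cent. For categorical outcomes it names the "X^2^-test or Fisher exact test for categorical data".

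Two other statements bear on the point. Allocation is equal ("Eligible patients will be randomized into the EPN group or the waitlist group in a 1:1 ratio with a variable block"). The Recruitment strategies section gives the timing of follow-up as "24-week follow-up (week 7–30", which is after the primary endpoint.

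**The concern.** Dividing a sample size by one minus the dropout rate suits an analysis of patients with data: 61 are recruited, about 49 remain, and the assumed rates apply to those 49. It does not suit an analysis in which every missing patient is a failure. There the denominator stays at 61, and each arm's response rate shrinks by its missing fraction. The difference to be detected shrinks as well, and recruiting 61 instead of 49 does not make up for that.

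At stake is the false-negative risk of the only primary test. A reader takes it to be 20%; under the protocol's own dropout figure it could be about 28%. The 27-point difference would also not be the quantity that the planned analysis estimates. The validity of the comparison and its type I error are not affected.

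**Working it through.** **Inputs.** From Sample size calculation: p1 = 0.55, p2 = 0.28, two-sided 5%, power 80%, 49 per arm, 20% drop-off, 61 per arm. From Randomization and allocation concealment: 1:1. From Statistical analysis: missing at week 6 = non-response. The z values are 1.960 and 0.8416, so (1.960 + 0.8416)² = 7.849.

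**Step 1: reproduce the plan's figures.** Unpooled formula:

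n = 7.849 × (0.55×0.45 + 0.28×0.72) / 0.27² = 7.849 × 0.4491 / 0.0729 = 48.35, so 49 per arm.

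This matches. Power at 49 per arm is 80.5% with this formula and 78.3% with the pooled-variance formula. For the inflation, 49/0.80 = 61.25, stated as 61; and 61 × 0.80 = 48.8, so the step restores about 49 evaluable patients. The rounding is trivial.

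**Step 2: apply the non-responder rule with 20% missing in each arm.** This assumes that 55% and 28% are rates among patients with data.

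- EPN: 0.55 × 0.80 = 0.440
- Waitlist: 0.28 × 0.80 = 0.224
- Difference: 0.216, against 0.27 planned

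Unpooled power at 61 per arm: SE = √[(0.44×0.56 + 0.224×0.776)/61] = √(0.42022/61) = 0.0830. Then 0.216/0.0830 − 1.960 = 0.642, and Φ(0.642) = 74.0%.

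Pooled power: the mean rate is 0.332 and the null SE is √(2×0.332×0.668/61) = 0.0853. Then (0.216 − 1.960×0.0853)/0.0830 = 0.589, and Φ(0.589) = 72.2%. Exact enumeration for the Pearson chi-square test also gives 72.2%.

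**Step 3: vary the share missing at week 6** (61 per arm, equal in both arms, same formulas).

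| Missing at week 6 | Analysed rates | Power, pooled | Power, unpooled |
|---|---|---|---|
| 0% | 55.0% vs 28.0% | 86.6% | 88.2% |
| 5% | 52.3% vs 26.6% | 83.5% | 85.2% |
| 10% | 49.5% vs 25.2% | 80.0% | 81.8% |
| 12% | 48.4% vs 24.6% | 78.5% | 80.3% |
| 15% | 46.8% vs 23.8% | 76.2% | 78.0% |
| 20% | 44.0% vs 22.4% | 72.2% | 74.0% |

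Power reaches 80% only up to about 10% missing (pooled) or 12% (unpooled). The 0% row also describes the case where 55% and 28% already count missing patients as failures; exact chi-square power there is 87.3%.

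**Step 4: unequal missingness** (illustrative assumptions, not from the documents; pooled formula). With 25% missing in EPN and 15% in waitlist, power is about 54%. With 15% in EPN and 25% in waitlist it is about 86%.

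**Step 5: size needed for 80% power at 20% missing.** Unpooled: 7.849 × 0.42022 / 0.216² = 70.7, so 71 per arm. Pooled: 74 per arm. No further inflation would apply, because missing patients stay in the denominator.

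**The case against.** The strongest objection is timing. The 20% is described as loss in the follow-up, which the article defines as weeks 7–30. A patient lost then has a week-6 diary and is not imputed as a failure, so the text does not say that 20% will be missing at week 6. This stands, and it makes the 72–74% conditional. It does not rescue the paragraph: the only dropout figure given is applied to a calculation for the week-6 endpoint. If that loss falls after week 6, the inflation is not needed for the primary endpoint.

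Second, the 55% and 28% come from previous research that is not available here and may already count missing patients as failures. That also stands. Power at 61 per arm would then be about 87%, and 122 patients would be a conservative number.

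Third, the 80% is attached to 49 per arm, where it reproduces; no power is stated for 61. True, but the purpose of the inflation is to keep that power after loss, and under the planned analysis it does not do so.

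Fourth, part of the gap to 72% is a change of formula. On the plan's own unpooled formula the fall is from 80.5% to 74.0%, about 6 points. Both figures are therefore given. A Fisher exact test would give 65.7%, but with 61 per arm and these rates the expected cell counts do not call for it, so that figure should not carry the argument.

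From all this a reader might infer that the trial simply has 72% power, or that no reading of the text is compatible with 80%. The document supports neither. About 10–12% missing at week 6 gives 80%, and less missing gives more.

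**Conclusion.** The point holds as an inconsistency between two stated elements: the inflation presumes that dropouts leave the analysis, and the primary analysis keeps them in as failures. The arithmetic of 49 and 61 is correct in itself. What is not secured is 80% power for the analysis as planned.

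The shortfall is about 6 to 8 points below 80% under three assumptions: 55% and 28% are rates among patients with data, the full 20% is missing at week 6, and missingness is equal in both arms. The inflation implies the first. The document states neither the second nor the third. If the first or second fails in the way the objections describe, there may be no shortfall. Non-responder imputation is a legitimate choice and is not in question; its effect on power has not been carried into the sample size paragraph.

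**What to change.** Keep 122 patients and the non-responder rule, and rewrite the Sample size calculation paragraph to match the planned analysis:

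1. State whether 55% and 28% are rates among patients with data or already count missing patients as failures.
2. State the share expected to be missing at week 6, separately from loss in weeks 7–30, and whether it is assumed equal in both arms.
3. Restate the power at 61 per arm accordingly: about 72–74% with 20% missing at week 6, about 80% with 10%, and about 87% with none or if the rates already include missing as failure. Name the formula or test used.
4. Under the last reading, drop the inflation as a rationale for the primary endpoint.

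The cost is one paragraph of wording. No extra patients, change of test or change of endpoint is needed to correct the statement. The drawback is that the stated power may be less favourable. If the sponsor wants 80% with 20% missing at week 6, about 71 to 74 per arm (142 to 148 in total) would be required, which is a separate decision.

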### Statistical analysis

2.9

The primary outcome of 24-hour mean HF score will be compared between the EPN group and the waitlist control group at week 6. Those who did not feedback data of HF score at week 6 will be regarded as patients whose reduction does not reach 50%. A *P* value <.05 will be considered statistically significant. Subgroup analysis will be conducted among perimenopausal patients and postmenopausal patients.

Continuous data will be presented as mean ± standard deviation when normally distributed, or be presented as median (interquartile range) when not normally distributed. Categorical data will be presented as the number and percentage of participants. Statistical comparisons will be performed by Student *t* test or Wilcoxon rank sum test for continuous data and by X^2^-test or Fisher exact test for categorical data. Data will be analyzed using SPSS software V.22.0 (IBM SPSS Statistics; IBM Corp, Somers, NY).

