##### Secondary outcome measure

2.8.3.2

1.The proportion of patients with a reduction of 50%^[17]^ or more on the mean 24-hour HF score from baseline at weeks 3, 18, and 30.2.The proportion of patients with a reduction of 50% or more on the mean 24-hour HF frequency from baseline at weeks 3, 6, 18, and 30. The mean 24-hour HF frequency will be calculated based on the number of HF recorded in 7-day HFD, as follows: mean 24-hour HF frequency = total number of HF reported/number of days reported.3.The proportion of patients with at least a 50% reduction in the mean 24-hour HF severity from baseline at weeks 3, 6, 18, and 30. The mean 24-hour HF severity will be calculated based on the frequency of HF and the severity of each HF recorded in 7-day HFD, as follows: mean 24-hour HF severity = (1 × number of mild HF + 2 × number of moderate HF + 3 × number of severe HF + 4 × number of very severe HF)/number of HF reported.4.The changes in the mean 24-hours HF score^[17]^ from baseline at weeks 3, 6, 18, and 30. A decrease of 5.35 episodes in moderate and severe HF per day from baseline has been reported as minimal clinically important difference (MCID).^[18]^5.The changes of MRS score from baseline at weeks 6, 18, and 30. MRS is a menopause-specific subscale commonly used for Chinese women. It includes 11 items concerning psychological, somatic, and urogenital domains.^[19]^ The scores of MRS range from 0 (best) to 44 (worst), and an increase of 5 points is regarded as the MCID).^[20]^6.The changes of MENQOL score from baseline at weeks 6, 18, and 30. MENQOL is a validated measurement of the quality of life and clinical symptom changes during the menopausal transition and the first 8 years postmenopause.^[21]^ It consists of 29 items to assess the 4 domains of vasomotor symptoms, physical symptoms, psychological symptoms, and urogenital/sexual symptoms. The total score of MENQOL ranges from 0 (best) to 174 (worst), with a reduction of 4 points as MCID.^[21–22]^7.The proportion of participants reporting “significantly reduced” or “moderately reduced” based on Global Response Assessment at weeks 3, 6, 18, and 30. The responses of participants to the treatments are divided into 7 grades of Global Response Assessment: significantly reduced, moderately reduced, slightly reduced, no change, slightly aggravated, moderately aggravated, and significantly aggravated. The proportion of participants reporting “significantly reduced” or “moderately reduced” are recorded as the response rate of overall efficacy.8.Patients’ acceptability toward EPN at the end of the 1st and 9th treatments. The acceptability toward EPN will be assessed among participants in the EPN group using a 3-point index: unacceptable (0 points), acceptable (1 point), and easy to accept (2 points). Those who regard EPN unacceptable will report the reasons. The average score will be calculated after the 2 assessments.9.Expectations and confidence of patients in the EPN group at baseline. Patients in the EPN group will answer the following questions before the first intervention: “Do you think acupuncture is effective for treating the disease?” and “Do you think acupuncture is effective in alleviating menopausal associated HF?” The participants can answer “Yes,” “No,” or “Unclear.”

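### Changes in HF score, MRS and MENQOL are compared by unadjusted two-sample tests although each baseline value is collected; ANCOVA would usually be more precise at almost no cost

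*Protocol article*

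**What the plan says.** Section 2.9 fixes the tests by type of data: Student t test or "Wilcoxon rank sum test for continuous data", and chi-square or "Fisher exact test for categorical data". It names no covariate, regression model or stratified test.

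The continuous outcomes in section 2.8.3.2 are changes from baseline in HF score (weeks 3, 6, 18 and 30), in MRS, and in MENQOL ("The changes of MENQOL score from baseline at weeks 6, 18, and 30"). Table 1 and section 2.2 show the HF diary, MRS and MENQOL all taken at baseline. Section 2.2 also records menstrual information, and section 2.9 uses menopausal status to define subgroups. Section 2.3 describes 1:1 randomization in variable blocks and names no stratification factor.

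The primary outcome is binary. Section 2.8.3.1 defines it, and section 2.8.3.4 powers it, as the proportion with a "reduction of 50% or more on their mean 24-hour HF score from baseline at week 6".

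**The concern.** Baseline enters the continuous comparisons only by subtraction. That forces a slope of 1 of follow-up on baseline, whatever the data show. Where the true slope is below 1, the change score over-corrects: it carries extra noise, and an arm that happens to start higher will appear to improve more. Nothing named in the randomization balances baseline severity or menopausal stage, so in a trial of 122 a visible chance difference is quite possible.

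At stake are the width of the intervals for the three continuous secondary outcomes and their robustness to such a difference. Because section 2.9 states which tests will be used, this is a choice that can be improved. It is not a detail left to another document.

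**Working it through.** **The plan's own figure.** Inputs from section 2.8.3.4: 55% against 28%, two-sided 5%, 80% power. The unpooled formula gives (1.960 + 0.842)² × (0.55×0.45 + 0.28×0.72) / 0.27² = 48.35, so 49 per arm, as stated. Allowing for 20% dropout, 49/0.8 = 61.25, against 61 stated. The sample size rests on an unadjusted comparison of proportions, and no continuous outcome is powered.

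**Precision for the continuous outcomes.** The documents give neither ρ nor an SD, so ρ is assumed. With equal SDs at baseline and follow-up, and in units of that variance, the large-sample variance factor is 2(1−ρ) for a change-score t test and 1−ρ² for ANCOVA. Their ratio is (1−ρ²)/[2(1−ρ)] = (1+ρ)/2.

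| Assumed ρ | Change score | ANCOVA | Ratio | Interval narrower by | Extra patients, 1/ratio − 1 | 49 per arm worth about |
|---|---|---|---|---|---|---|
| 0.3 | 1.40 | 0.91 | 0.65 | 19% | 54% | 75 |
| 0.5 | 1.00 | 0.75 | 0.75 | 13% | 33% | 65 |
| 0.7 | 0.60 | 0.51 | 0.85 | 8% | 18% | 58 |

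The variance falls by 35% to 15%. The equivalent gain in patients is the reciprocal, 54% to 18%. Where a change-score test with 49 per arm had 80% power, ANCOVA would have about 94%, 90% and 86%. At ρ = 0.8 the ratio is 0.90, worth about 11% more patients.

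**Dependence on equal variances.** In general the change-score variance exceeds the ANCOVA variance by (SD_baseline − ρ × SD_follow-up)². This is never negative, but it is zero when ρ × SD_follow-up / SD_baseline = 1. For example, with SD_follow-up = 1, SD_baseline = 0.5 and ρ = 0.5, the change score has variance 1 + 0.25 − 0.5 = 0.75 and ANCOVA has 1 − 0.25 = 0.75, so there is no gain. The entry threshold on hot flashes in section 2.6 may narrow the baseline spread of HF score. If so, the gain for that outcome would be smaller than the table shows.

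**Chance imbalance.** With equal variances, a change-score comparison keeps (1−ρ) times the baseline difference D. With 61 per arm, 95% of chance differences lie within 1.96 × √(2/61) = 0.355 SD. That leaves up to 0.25, 0.18 and 0.11 SD at ρ = 0.3, 0.5 and 0.7. With 49 per arm the limit is 0.396 SD, leaving up to 0.28, 0.20 and 0.12 SD. ANCOVA removes this term when its linear model holds.

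**The binary primary.** The ratio above does not apply to it. A simulation with 49 per arm at 55% and 28% (3,000 runs per setting) compared chi-square with a logistic likelihood-ratio test adjusted for one baseline covariate. The latent correlation of covariate with response was assumed.

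| Assumed latent correlation | Chi-square power | Adjusted power |
|---|---|---|
| 0 | 79.2% | 79.5% |
| 0.2 | 79.6% | 81.0% |
| 0.3 | 79.0% | 82.0% |
| 0.4 | 79.2% | 83.7% |
| 0.5 | 78.4% | 84.8% |

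The gain is 0 to about 6 points. The Monte Carlo standard error of each power is about √(0.8×0.2/3000) = 0.7 points.

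**The case against.** The strongest reply is that this is a preference for efficiency. Under randomization the t, Wilcoxon, chi-square and Fisher tests keep their type I error and are unbiased on average. The trial is sized for an unadjusted test of proportions, and the size of any gain rests on a correlation that the documents do not supply. All of this stands. It limits the point to precision and conditional balance, and mainly to secondary outcomes. It does not remove the point, because the baseline values are already collected and using them is close to free.

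A reader might infer more, and the documents do not support it:

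- **That baseline is ignored.** The continuous outcomes are changes from baseline, and the HF responder outcomes are percentage reductions from it. Menopausal status is used for subgroups.
- **That every outcome is affected.** The Global Response Assessment has no baseline value, and acceptability and expectation are collected in the EPN group only.
- **That change scores always lose whenever ρ is below 1.** With unequal variances the loss can be nil, as shown in the working.
- **That subgroups will be judged by separate P values.** Section 2.9 says "Subgroup analysis will be conducted among perimenopausal patients and postmenopausal patients" and specifies no test. It neither plans within-stratum P values nor rules out an interaction test.
- **That section 2.9 makes the mean score the primary outcome.** It does say "The primary outcome of 24-hour mean HF score will be compared between the EPN group and the waitlist control group at week 6". But its next sentence counts patients without week-6 data as not reaching a 50% reduction, which makes sense only for the responder outcome, and sections 2.8.3.1 and 2.8.3.4 agree. This is loose wording.

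**Conclusion.** The point holds as a recommendation about efficiency. For the changes in HF score, MRS and MENQOL, the stated t or Wilcoxon test is valid but usually less precise than ANCOVA. With equal variances and an assumed ρ of 0.3 to 0.7, the ANCOVA variance is 0.65 to 0.85 of that of the change-score t test, equivalent to about 54% to 18% more patients. The same change removes the residue of chance baseline imbalance, which could reach 0.25 to 0.11 SD with 61 per arm. These figures are for the t test. The Wilcoxon test also uses baseline only by subtraction, but the ratio was not derived for it.

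For the week-6 responder primary the expected gain is modest, 0 to about 6 points of power under assumed correlations. The chi-square analysis need not be displaced.

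**What to change.** In section 2.9:

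1. Analyse HF score, MRS and MENQOL by ANCOVA at each visit, or by a mixed model with an arm-by-visit term. Fix the outcome's own baseline value and menopausal status in advance as covariates.
2. For the week-6 responder primary, keep the chi-square test. Optionally add a prespecified logistic model with arm, baseline HF score and menopausal status, reported as a standardized risk difference with a 95% confidence interval. State in advance which of the two is the primary analysis.
3. While editing the section, name the primary outcome as the proportion with at least a 50% reduction, to match sections 2.8.3.1 and 2.8.3.4.

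The cost is analysis wording only. HF score, MRS and MENQOL are already measured at baseline, menopausal status is already needed for the subgroups, and neither the sample size nor the visit schedule changes.
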